### Eligibility Criteria

The inclusion criteria are as follows: (1) age 40 to 65 years, (2) able to understand and follow study instructions, (3) able to communicate coherently and oriented to time and place, (4) provided written informed consent, (5) stroke ≥6 months prior to enrollment (chronic stroke), (6) ankle plantarflexor spasticity ≤2 on the Modified Ashworth Scale [15], (7) ankle dorsiflexor strength ≥grade 2 on the Medical Research Council scale [15], (8) passive ankle dorsiflexion to neutral (90°; 0°) without a plantarflexion contracture [15], (9) moderate or mild lower-extremity impairment based on the Fugl-Meyer Assessment–Lower Extremity (FMA-LE) score (21‐27, moderate; and 28‐34, mild or good) [36], (10) able to sit for at least 1 hour [37], (11) able to walk at least 10 m with or without an assistive device [20], and (12) completed all conventional lower-extremity physical therapy and rehabilitation programs.

The exclusion criteria are as follows: (1) cognitive impairment (Mini-Mental State Test score ≤24); (2) conditions affecting walking or balance (eg, orthopedic complications, lower-extremity amputation, and osteoporosis) [22]; (3) insufficient visual acuity to view a screen (eg, diplopia) [22]; (4) severe visual deficits (eg, hemianopia) or vestibular disorders [32]; (5) sensory deficits such as hemisensory neglect; (6) acute musculoskeletal or cardiovascular disorders [23]; (7) intrathecal baclofen pump use or botulinum toxin injections within the past 5 months [23]; (8) fixed or painful contracture of the paretic ankle [12,24]; (9) uncontrolled systemic diseases (eg, diabetes, hypertension, and debilitating or immunosuppressive diseases) [15]; (10) history of a nonstroke neurological disease or disorder that may impair comprehension of instructions; and (11) concurrent participation in other lower-extremity physical therapy, robotic rehabilitation, or neurological exercise programs.

### Sample Size

On the basis of the post-intervention walking speed values reported by Cho et al, mean 1.22 (SD 0.33) m/s in the robot-assisted ankle muscle training group, and mean 0.84 (SD 0.29) m/s in the control group, the estimated effect size was Cohen *d*=1.21. Using G*Power 3.1 (version 3.1.9.7; Heinrich Heine University Düsseldorf) for an independent samples *t* test, with a 2-tailed α level of .05, 95% power, and an allocation ratio of 1:1, the required sample size was calculated as 19 participants per group. Therefore, the total sample size was revised to 38 participants.

### Sequence Generation and Allocation Concealment

Randomization will be implemented using a centralized computer-based system (Study Randomizer; Phase Locked Software) by a research coordinator who is not involved in referral, intervention delivery, or outcome assessment. Stratified permuted block randomization will be used to balance groups according to baseline FMA-LE severity (0‐20, severe; 21‐27, moderate; and 28‐34, mild or good) [36] and affected hemisphere (right or left). Within each stratum, participants will be allocated 1:1 using fixed block sizes (block size=4; final block=2 if required). Following eligibility confirmation and completion of baseline assessments, participant details will be entered into the system, which will automatically generate the allocation. The allocation sequence will be concealed within the centralized system; enrolling and treating personnel will not have access to the randomization lists or assignment order, preventing prediction or manipulation of allocations.

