### Blinding

This study will be single blind (assessor blinded). Outcome assessments will be performed by a trained research assistant blinded to group allocation and not involved in referral, randomization, intervention delivery, or trial coordination. Due to the nature of the intervention, participants and the treating physiotherapist cannot be blinded.

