### Ethical Considerations

#### Research Ethics Approval

The initial study protocol, informed consent forms, and study-related documents were approved by the Istanbul Medipol University Clinical Research Ethics Committee (approval E-66291034‐202.3.02-8175) on December 4, 2025. The current approved protocol is version 4, dated January 2026, and was approved by the same ethics committee on January 14, 2026. Written informed consent will be obtained from all participants before enrollment. The consent process will be conducted by physiotherapists trained in research ethics and legal requirements; participants will have the opportunity to ask questions before signing. The study is registered at ClinicalTrials.gov (identifier: NCT07091045). Study findings will be disseminated through peer-reviewed publications and scientific conference presentations.

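### Fixed, published blocks of 4 within strata let staff who track unblinded assignments deduce roughly 28-32% of allocations, so withholding the lists does not by itself prevent prediction

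*Protocol article*

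**What the plan says.** All places are in the protocol article.

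- **Block scheme** (Sequence Generation and Allocation Concealment): "Within each stratum, participants will be allocated 1:1 using fixed block sizes (block size=4; final block=2 if required".
- **Claim about concealment** (same section): "enrolling and treating personnel will not have access to the randomization lists or assignment order, preventing prediction or manipulation of allocations". A coordinator outside referral, delivery and assessment runs the central system. The allocation is generated once eligibility is confirmed and baseline assessments are done.
- **Blinding**: "participants and the treating physiotherapist cannot be blinded". The outcome assessor is blinded and has no part in referral, randomization or delivery.
- **Consent** (Research Ethics Approval): "The consent process will be conducted by physiotherapists trained in research ethics and legal requirements". Nothing says whether these physiotherapists also treat.
- **Strata** (Sequence Generation and Allocation Concealment): "baseline FMA-LE severity (0‐20, severe; 21‐27, moderate; and 28‐34, mild or good" crossed with "affected hemisphere (right or left", which makes 3 × 2 = 6 cells.
- **Eligibility Criteria**: "moderate or mild lower-extremity impairment based on the Fugl-Meyer Assessment–Lower Extremity (FMA-LE) score", given as 21-27 or 28-34.
- **Statistical Analysis**: both stratification variables enter the ANCOVA as covariates.

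**The concern.** Keeping the list hidden stops staff from looking up the next assignment. It does not stop them from working it out. In a permuted block of known size, once one arm has its full share, every remaining place goes to the other arm. Robot and manual training cannot be confused, so treating staff see each assignment. Affected hemisphere is a known baseline fact, and FMA-LE is an eligibility criterion, so a candidate's stratum is known before randomization.

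If someone who influences enrolment also knows the tally, a participant with better or worse prospects can be approached, delayed or encouraged according to the expected arm. The Study Setting section plans appointments flexibly where possible, which leaves some room for timing. In a trial of 30 (Abstract) or 38 (Sample Size) participants, selection on prognostic features that the model does not measure would bias the walking-speed comparison.

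The rule for a final block of 2 adds to this. It is applied per stratum, although stratum totals are unknown until recruitment ends, and half of a block of 2 is certain to anyone who knows that it is in use.

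**Working it through.** **Inputs.** Block size 4, final block 2, ratio 1:1 (Sequence Generation and Allocation Concealment). Total N is 38 (Sample Size) or 30 (Abstract), so both are used. The article gives no predictability figure to reproduce; N only scales the result. The stated 19 per group does reproduce: with d = 1.21 and two-sided α = .05, exact t-test power is 94.1% at 18 and 95.2% at 19 per group.

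**Usable strata.** Eligibility removes FMA-LE 0-20, so 2 of the 6 listed cells are empty: 2 levels × 2 hemispheres = 4 strata.

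**Certain allocations in one complete block of 4** (6 equally likely orders of AABB):
- Places 1 and 2: never certain.
- Place 3: certain if the first two match, probability 2/6 = 1/3.
- Place 4: always certain.
- Sum: 1/3 + 1 = 4/3, and (4/3)/4 = 33.3%.

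In a block of 2 it is 1 of 2 = 50%.

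**Best guessing in a complete block of 4** (guess the arm that is behind; toss a coin if level):
- Place 1: 1/2.
- Place 2: 2/3.
- Place 3: (1/3)(1) + (2/3)(1/2) = 2/3.
- Place 4: 1.
- Sum: 17/6 = 2.83, and 2.83/4 = 71%.

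**Over four strata with incomplete last blocks** (simulation, 3,000 runs, equal strata; assumes perfect tracking and, where used, knowledge that a final block of 2 is running):

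| N | Rule | Certain | Number | Best guess correct |
|---|---|---|---|---|
| 38 | final block of 2 | 31.6% | 0.316 × 38 ≈ 12 | 69.7% |
| 38 | all blocks of 4 | 28.9% | 0.289 × 38 ≈ 11 | 68.9% |
| 30 | final block of 2 | 31.1% | 0.311 × 30 ≈ 9 | 69.4% |
| 30 | all blocks of 4 | 27.9% | 0.279 × 30 ≈ 8 | 68.3% |

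The central 95% of runs gave certain shares between about 20% and 40%. Strata of unequal size (35/35/15/15%) changed the means by about 0.1 percentage point or less.

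**Final block of 2.** 38 = 9 × 4 + 2 and 30 = 7 × 4 + 2, so one final block of 2 fits a single list of known length. Within four strata, the lengths are not known in advance.

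**Varying block sizes** (1,500 runs, strata of 8 and 10; the observer knows the possible sizes but not the current one):

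| Sizes | Certain | Best guess correct |
|---|---|---|
| 4 only | 27-33% | 68-71% |
| 2 and 4 | 9-10% | 71% |
| 4 and 6 | 6-7% | 67-68% |
| 2, 4 and 6 | 3% | 69% |

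Varying the sizes removes most of the certainty. It does little to the best-guess rate of an observer who knows the menu of sizes.

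**The case against.** The safeguards are real. Allocation comes from a central system run by an independent coordinator, only after eligibility and baseline are complete, so nobody can be screened out at the moment of assignment. The assessor is blinded, and the ANCOVA adjusts for baseline walking speed, FMA-LE severity and hemisphere. These points stand, but they do not close the gap. Whom to approach, and when, is decided before allocation; a blinded assessor measures a selected group faithfully; and adjustment does not reach unmeasured prognosis.

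The calculation also assumes a complete, ordered tally in each of four strata. That is demanding, so the percentages describe what could be deduced, not what will be.

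A reader might infer more than the documents support:
- **That consenting physiotherapists see the assignments, or that one small team does everything.** The article states neither. It describes two locations and several physiotherapists. It leaves overlap between consent and treatment open, which is a risk and no more.
- **That the empty 0-20 level could let in ineligible people or bias allocation.** Eligibility is confirmed first, by the physiatrist according to Oversight and Monitoring. An empty cell allocates nobody and adds no data to the ANCOVA. Nor does the article show that six cells were set up in the software.
- **That a person must step in to trigger the final block of 2.** The trigger is not described and may be automatic. What stands is that the rule needs a stratum total that is not known beforehand.

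**Conclusion.** The concern holds as a risk of selection bias; no breach is shown. The statement that prediction is prevented is too strong for fixed, published blocks of 4 under unblinded delivery. Staff who track assignments by stratum could know about 28-32% of allocations with certainty (33% in complete blocks) and guess about 68-71% correctly, against 50% by chance. The conclusion does not depend on whether N is 30 or 38. It rests on two assumptions: that past assignments are tallied accurately by stratum, and that whoever holds the tally can influence enrolment. The article neither confirms nor rules these out.

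The FMA-LE mismatch is a separate and minor inconsistency: a listed level that the eligibility criteria exclude. It has no effect on allocation.

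**What to change.** For allocations not yet made, have the independent coordinator:
1. Set randomly varying block sizes within each stratum, for example 2 and 4, or 4 and 6. In the check above, 4 and 6 did better on both certainty and guessing.
2. Keep the sizes from enrolling and treating staff, and out of any public document until recruitment closes.
3. Drop the per-stratum final block of 2.

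Soften the claim that prediction is prevented, and state whether those who take consent also treat. Reconcile the 0-20 FMA-LE level with the 21-34 eligibility range, so that the strata and the ANCOVA covariate use two FMA-LE levels by two hemispheres.

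**Cost.** A documented, versioned amendment, and confirmation that the randomization software allows the change during the trial, which the article does not show. Balance may be slightly worse: a stratum that stops mid-block can differ by at most half the block size, that is 2 for a block of 4 and 3 for a block of 6. Only four participants were enrolled by March 25, 2026, so 38 − 4 = 34 allocations (or 30 − 4 = 26) could be covered if the change had been made at that date; fewer if it comes later.

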### Blinding

This study will be single blind (assessor blinded). Outcome assessments will be performed by a trained research assistant blinded to group allocation and not involved in referral, randomization, intervention delivery, or trial coordination. Due to the nature of the intervention, participants and the treating physiotherapist cannot be blinded.

### Interventions

#### Overview

All participants will receive conventional rehabilitation for approximately 20 to 25 minutes, 3 days per week, for 6 weeks. The conventional program will include upper extremity mobilizations, trunk and upper extremity flexibility or positioning exercises for spasticity, and trunk and balance training in sitting [24].

In addition to the conventional program, participants will receive structured ankle-foot training. The RTG will undergo structured robot-assisted ankle-foot training, whereas the MTG will receive the same structured ankle-foot training protocol administered manually by a physiotherapist. Ankle-foot training sessions will last approximately 30 to 35 minutes, yielding a total session duration of 50 to 60 minutes for both groups when combined with conventional rehabilitation.

#### Robotic System

The BalanSENS robotic rehabilitation system will be used in the RTG. The system includes a fixed, platform-based end-effector ankle-foot robot featuring a parallel manipulator with a 3-degree-of-freedom rotary-prismatic-spherical configuration [38,39]. The usability of the system has been previously evaluated in healthy individuals [39].

#### Robot Design and Features

The system is designed for safe, comfortable seated rehabilitation. The height-adjustable, 180° rotatable chair integrated into the platform facilitates alignment of the participant with the robot. The chair and platform allow adjustment of hip-popliteal length, hip width, shoulder height, and the distance between the participant and the ankle-foot robot (Figure 2). The robot provides 3 degrees of freedom motion (2 rotational axes and 1 linear axis) to train ankle dorsiflexion-plantarflexion and inversion-eversion movements via the 3-degree-of-freedom rotary-prismatic-spherical parallel mechanism, enabling controlled dynamic loading of the ankle [38].

The system includes load cells, vibration motors, and a multiaxis motion platform. Load cells are calibrated using a second-order polynomial for force-voltage conversion, enabling patient-specific torque limits and ensuring a safe ROM [38]. Vibration motors (HUB360) positioned under each plantar region operate at 5 V direct current and provide haptic stimulation (0‐200 Hz frequency; 0%‐100% pulse width modulation duty cycle). A plantar map comprising 7 regions corresponding to motor locations is displayed on the integrated screen, allowing the participant to indicate the perceived stimulation location (Figure 3) [38].

**Figure 2. F2:**
[figure not shown]
BalanSENS platform and seated foot-ankle rehabilitation setup incorporating a 3-RPS parallel robot, with an illustrative representation of platform motion at different angles. 3-RPS: three-degree-of-freedom rotary-prismatic-spherical; VR: virtual reality.

**Figure 3. F3:**
[figure not shown]
Representation of foot pressure measurement and vibration motor assembly box mounted on the upper platform of the parallel robot: (A) top view of the assembly box, (B) 7 key plantar regions for placement of load cells and vibration motors, and (C) exploded view of the assembly for illustration.

The robot provides position control during passive ROM training and impedance control during active ROM training, allowing both passive and active practice. During passive training, the ankle follows a robot-defined trajectory; during active training, participants perform movement tasks at prescribed speeds with assistive or resistive support guided by visual instructions [40]. The platform-based system operates under an AAN paradigm, monitoring ankle kinematics and kinetics in real time and providing only the assistance required to complete the task. Task difficulty is individualized by adjusting platform stiffness, movement speed, and end-position holding duration (VR tasks).

Visual feedback will be provided throughout training using 2 VR-based games. The first VR game will be used during both passive and active ROM training. In this game, ankle dorsiflexion-plantarflexion is represented by the upward-downward motion of a bird to collect targets. During passive training, the bird’s movement follows the robot-driven ankle trajectory (Figure 4), whereas during active training, it is controlled by the participant’s ankle movement (Figure 5). The second VR game is specifically designed for JPS training, in which upward bird movement is linked to dorsiflexion to encourage active participation (Figure 6).

**Figure 4. F4:**
[figure not shown]
Virtual reality game interface for passive range of motion training, comprising 3 different environments.

**Figure 5. F5:**
[figure not shown]
Virtual reality game interface for active training: (1) a bird avatar representing ankle motion along the dorsiflexion–plantarflexion (DP) axis, (2) coins positioned along the movement trajectory to encourage continuous tracking, (3) diamonds placed at the calibrated range of motion (ROM) boundaries to promote full-range excursions, (4) right-to-left trajectory flow, (5) real-time score displaying collected coins and diamonds, (6) therapy parameters shown on-screen (cycle number, speed, and stiffness level), (7) a maximal ROM holding zone providing peak rewards, and (8) real-time plantar pressure distribution derived from footplate sensors.

**Figure 6. F6:**
[figure not shown]
Virtual reality game interface for joint position sense training: (A) the target angle is set and recorded by the system, (B) the robot moves the ankle to the target angle (passive positioning), and (C) the participant is asked to actively reproduce (match) the target angle.

#### Participant Positioning

##### RTG Position

Participants will be comfortably seated on a height-adjustable chair with back support, adjusted so that the hip-knee angle is approximately 90° in accordance with ergonomic criteria. The paretic foot will be placed on a footplate, and the nonparetic foot on a footrest matched to the plate’s height. The paretic foot will be secured using a Velcro strap. A monitor providing interactive VR-based visual feedback will be positioned at the participant’s eye level.

##### MTG Position

Throughout all training stages, participants will be positioned in the long-sitting position with the knee supported at approximately 30° to 45° of semiflexion. This position is intended to ensure balanced muscle-tendon tension and safe implementation of the interventions [41]. As the manual training is delivered without robotic fixation and alignment constraints, long sitting is used to facilitate consistent therapist handling across stages.

### Robot-Assisted Training Protocol

#### Overview

The experimental procedure will consist of a structured, robot-assisted ankle-foot training protocol. The protocol comprises (1) plantar vibrotactile sensory training, (2) passive ROM training, (3) VR-integrated JPS training, (4) active ROM training under an AAN paradigm with real-time adjustment based on VR game performance, and (5) repetition of plantar vibrotactile sensory training.

During robot-assisted training sessions, surface electromyography (sEMG) from the tibialis anterior and gastrocnemius will be monitored in real time on-screen together with load-cell signals to support session supervision and safety (eg, detection of excessive cocontraction or abnormal effort). sEMG monitoring will be used for clinical oversight during training and will not be used as an efficacy outcome.

The training stages and progression are described below.

#### Stage 1: Sensory Education—Plantar Vibration and Sensory Localization Training

The current literature suggests that plantar vibration in people with stroke may positively affect balance, gait, and proprioceptive feedback. However, due to heterogeneity in stimulation parameters, there is no consensus on optimal frequency and amplitude [27]. In people with stroke, plantar interventions have commonly been applied at 80 to 100 Hz [28,42]. In vibrating insoles or wearable systems used during walking, higher frequencies (eg, 200‐250 Hz) have been used to enhance proprioceptive stimulation [42].

In the first part of stage 1, vibration parameters will be individualized based on sensory tolerance. Individual perception and discomfort thresholds will be determined prior to training. The stimulation frequency will initially be set at 80 Hz, and vibration intensity will be gradually increased by adjusting the pulse width modulation duty cycle from 0% to 100%. The clinical stimulation intensity will be selected slightly below the discomfort threshold while still providing a clearly perceived somatosensory stimulus. Following threshold determination, a brief frequency scan (80, 100, 120, and 150 Hz) will be performed at the selected stimulation intensity, and the frequency at which the participant reports perceiving the vibration most clearly will be recorded as the preferred frequency. During training, plantar vibration will be applied within the 80 to 150 Hz range for all participants, with stimulation intensity individualized according to each participant’s sensory tolerance. After determining threshold parameters, all plantar vibration motors will be activated to provide stimulation for 3 minutes, delivered in consecutive cycles of 10 seconds of vibration followed by 5 seconds of rest.

In the second part of stage 1, vibration will be combined with sensory localization training. A 7-zone plantar map corresponding to vibration motor locations will be displayed on the integrated screen (Figure 3). The participant will indicate the perceived stimulation zone using a wireless mouse. Each set will consist of 12 stimulation sequences randomly selected from the 7 plantar zones (eg, 1-7-5-3-1-2-4-6-5-7-3‐4). Each stimulation will be delivered for the planned stimulus duration (Table 2), followed by a fixed 5-second rest or response period with no additional stimulation, during which the participant identifies the perceived zone. Correct responses and reaction times will be recorded as monitoring indicators to track sensory-performance progression throughout training (not as outcome measures). Progression at this stage will be achieved by gradually reducing stimulus duration and increasing the number of sets (Table 2).

**Table 2. T2:** Progression of training stages for both groups.

Stage and parameter	Weeks 1 and 2	Weeks 3 and 4	Weeks 5 and 6
Sensory localization training			
Stimulation duration	5 seconds	4 seconds	3 seconds
Number of sets	1 set (12 randomized points)	2 sets (24 randomized points)	3 sets (36 randomized points)
Passive ROM^a^ training			
Position holding duration	5 seconds	10 seconds	15 seconds
Number of repetitions per set	2×10	3×10	4×10
JPS^b^ training			
Number of repetitions	5	7	9
Active ROM training			
Number of sets	5×7	7×7	9×7

a ROM: range of motion.

b JPS: joint position sense.

